### Strategies to improve adherence to interventions {11c}

The administration of drugs and the collection of blood and tissue samples will be closely monitored by our specialized staff at our center. They will maintain close communication with the treating nurse and surgeons and monitor the progress of the trial.

### Relevant concomitant care permitted or prohibited during the trial {11d}

All included patients will receive the same medical and surgical treatments in accordance with the diagnosis and treatment guidelines for aTAAD.

### Provisions for post-trial care {30}

The sponsor has insurance that covers damage to research subjects resulting from injury or death caused by ketorolac. This insurance applies to any damage that becomes apparent during the trial and the subsequent 90-day follow-up period.

### Outcomes {12}

#### Primary endpoint

Efficacy: death, organ malperfusion syndrome, permanent dialysis, tracheotomy, neurological impairment, postoperative mechanical circulatory support, and unplanned cardiac reoperation.

Safety: gastrointestinal ulceration, gastrointestinal bleeding, gastrointestinal perforation, postoperative hemorrhage (postoperative hemorrhage exceeding 1000 ml within 24 h), renal failure, liver failure, drug allergies, and other severe adverse events following drug administration.

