## Safety assessment

Ketorolac has been used in clinical practice for many years and is generally well tolerated. According to the medication instructions, the primary adverse reactions associated with ketorolac are gastrointestinal reactions, gastric bleeding, and potential liver and kidney damage. Guidelines from the AHA suggest that ketorolac may also contribute to hypertension and kidney damage [16]. And some cardiovascular adverse events related to ketorolac should be included. Therefore, the safety assessment variables include death, organ malperfusion syndrome, hypertension (blood pressure > 140/90 mmHg), stage 2 AKI diagnosed by KIDGO criteria [18], tracheotomy, neurological impairment prior to discharge, postoperative mechanical circulation support, and postoperative cardiac arrest.

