### Sample size {14}

The required sample size was calculated using the PASS (15.0.5) software. The primary endpoint of efficacy was used to calculate the sample size. In the literature, the total death rate of hospitalization after surgery was 25% [7], the incidence of organ malperfusion syndrome was 15–33% [19, 20], permanent dialysis was 2.6% [21], tracheotomy was 8% [22], neurological impairment was 6.9% [22], postoperative mechanical circulatory support was 20% [23], unplanned cardiac reoperation was 4.2% [24], and postoperative cardiac arrest was 0.7–5.2% [25]. Therefore, we assumed that the incidence of composite endpoint events in the control group is 70%, and the incidence of composite endpoint events in the ketorolac group is reduced to 40%. Using PASS (15.0.5) software, when the sample size of the ketorolac group and the control group is 53 cases, this difference can be detected with over 90% confidence. Considering that the loss of follow-up rate is higher than 10%, the final total sample size of this experiment is 120 cases, with 60 cases in the experimental group and 60 cases in the control group.

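### The open-ended last item of the primary safety composite is defined by timing alone, so efficacy events can enter it and mask harm; other sections conflict on whether they should

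*Protocol article*

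**What the plan says.** Under Outcomes, the protocol article gives the primary endpoint two halves.

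- **Efficacy:** death, organ malperfusion syndrome, permanent dialysis, tracheotomy, neurological impairment, postoperative mechanical circulatory support and unplanned cardiac reoperation.
- **Safety:** gastrointestinal ulceration, bleeding and perforation, postoperative haemorrhage over 1000 ml in 24 h, renal failure and liver failure, ending with "drug allergies, and other severe adverse events following drug administration".

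Three other places bear on what that last item means.

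- **Abstract (Methods/design) and Intervention description:** the first injection is given before surgery. The abstract also describes the primary endpoint as a composite concerning drug-related adverse events.
- **Safety assessment:** "the safety assessment variables include death, organ malperfusion syndrome", followed by hypertension, stage 2 AKI, tracheotomy, neurological impairment before discharge, mechanical circulation support and cardiac arrest.
- **Sample size:** "The primary endpoint of efficacy was used to calculate the sample size". For that endpoint, "we assumed that the incidence of composite endpoint events in the control group is 70" per cent, and "the incidence of composite endpoint events in the ketorolac group is reduced to 40" per cent. No rate is given for the safety composite or for any named harm.

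**The concern.** An event qualifies for the last safety item if it is severe and comes after study drug. Since drug is first given before the operation, every postoperative death, malperfusion, tracheotomy, neurological impairment, mechanical support and reoperation meets that description. Nothing in the item requires the event to be related to the drug, and nothing removes events already counted under efficacy.

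If those events are counted, the safety composite is largely the efficacy composite with the named harms added. A treatment that lowers efficacy events would then lower the safety composite too, whatever it does to bleeding, ulceration, kidney or liver. The comparison meant to show whether ketorolac causes those harms could miss them, or point the other way. This matters because the Discussion says that, if the hypothesis holds, ketorolac can be considered safe in this population.

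**Working it through.** **1. The plan's own figure.** Two proportions, two-sided 5%, 90% power, unpooled variance:

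n = (1.960 + 1.282)² × (0.7×0.3 + 0.4×0.6) / 0.3² = 10.51 × 0.45 / 0.09 = 52.6, so 53 per arm.

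This matches the article ("when the sample size of the ketorolac group and the control group is 53 cases"). With 10% loss, 53/0.9 = 58.9, so 59, rounded to 60 per arm. The sample size is not in dispute. It shows that 70% v 40% is an assumption about efficacy events only.

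**2. Overlap of the lists.** Of the seven efficacy components, five (death, malperfusion, tracheotomy, neurological impairment, mechanical support) also appear under Safety assessment. Permanent dialysis and unplanned reoperation do not.

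**3. Model.** A patient has a safety event if a named harm occurs or a counted efficacy event occurs. Let e be the efficacy rate (70% placebo, 40% ketorolac), h the named-harm rate, and f the share of efficacy events that the last item captures. With h independent of e:

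safety composite = 1 − (1 − f·e)(1 − h)

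The values of h and f, and the independence, are assumptions. The test is the Pearson chi-square, two-sided at 0.05, as in Statistical methods. Probabilities are exact, from enumerating both binomial distributions.

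**4. Main case: h = 10% v 20%, f = 100%.**

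- Placebo: 1 − 0.30×0.90 = 0.73
- Ketorolac: 1 − 0.60×0.80 = 0.52

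Expected counts are about 44/60 v 31/60 (Pearson p = 0.014, Fisher p = 0.023), in favour of ketorolac. The named harms alone would be 6/60 v 12/60, p about 0.13, pointing to harm.

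**5. Range, 60 per arm.**

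| Named harms | Efficacy events counted | Composite, placebo v ketorolac | Significantly favours ketorolac | Significant harm, composite | Significant harm, named harms alone |
|---|---|---|---|---|---|
| 10% v 20% | 100% | 73% v 52% | 67% | <0.1% | 33% |
| 20% v 40% | 100% | 76% v 64% | 31% | <0.1% | 68% |
| 10% v 30% | 100% | 73% v 58% | 41% | <0.1% | 80% |
| 10% v 20% | 75% | 57.25% v 44% | 32% | <0.1% | 33% |
| 10% v 20% | 50% | 41.5% v 36% | 9% | 0.5% | 33% |
| 10% v 30% | 50% | 41.5% v 44% | 1% | 5% | 80% |

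At the 53 evaluable per arm that the plan targets, the first row gives 62.5% instead of 67%.

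**6. Other assumptions, first row.**

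- Dependence: if harms fall only on patients without an efficacy event, 67% becomes 68%; if they fall wholly within patients who have one, 92%.
- Size of benefit: with efficacy at 70% v 50% it is 33%; at 70% v 60%, 9%; at 70% v 70%, 1%, and the composite then points to harm (73% v 76%).

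**The case against.** The strongest reply is that the safety list is a list of drug toxicities, set directly after an efficacy list to which death, malperfusion and the rest have just been assigned. Read that way, the last item means further toxicities of the same kind, and the abstract's reference to drug-related events supports it. The Safety assessment list stands under its own heading, contains items found in neither half of the primary endpoint (hypertension, stage 2 AKI, cardiac arrest), and is never said to feed the primary safety composite. This stands: that efficacy events are counted is an inference from the wording, not something the article states. What remains is that the operative definition uses timing, the abstract uses relatedness, and the two select different events.

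A second reply is that the reversal needs several things at once: nearly all efficacy events counted, a benefit close to the full 30 points, and a moderate named-harm rate. This also stands, as steps 5 and 6 show.

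A third is that harm would not be invisible. Adverse events are all recorded and graded, laboratory, drainage and transfusion data are secondary endpoints, and a monitoring board reviews safety. That is correct and limits the damage. It does not repair the primary safety comparison itself.

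**Conclusion.** The definition should be fixed. As worded, the last item lets efficacy events into the safety composite, and the abstract, Outcomes and Safety assessment do not agree on whether they belong there.

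A reader might infer that the safety composite certainly contains the whole efficacy composite and that the trial will therefore report ketorolac as safer while its harms double. The documents do not support that. Inclusion is one of two available readings, the named-harm rates are not given, and the 67% figure depends on full capture and on the plan's full efficacy benefit.

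Masking is the more robust consequence. With named harms tripled (10% v 30%) and only half the efficacy events counted, the composite is nearly level at 41.5% v 44%. The chance of detecting harm is then about 5%, against 80% for the named harms alone. This too assumes independence and the plan's 70% v 40%.

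**What to change.** In Outcomes, do one of two things:

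- restrict the primary safety composite to the seven named harms; or
- keep the last item, but state that it excludes every component of the efficacy composite.

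Then reconcile the abstract, Outcomes and Safety assessment so that all three describe the same safety endpoint. Report the named harms as their own composite. Tabulate all other severe adverse events by arm, with efficacy components shown separately.

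Neither option fully separates the two halves. Renal failure overlaps permanent dialysis, and a haemorrhage over 1000 ml that leads to reoperation counts in both. The text should say so.

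The cost is wording only, since adverse events are already recorded and graded. Trial status reports 55 patients included and an interim analysis is planned at 60, so the wording should be settled before any unblinded comparison.

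The price is a lower event rate: at 10% v 20% and 60 per arm, the named-harm composite shows significant harm only about 33% of the time. If the last item is removed altogether, unexpected harms appear only in the adverse-event table.

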#### Secondary endpoints

Erythrocyte sedimentation rate (ESR), C-reactive protein, procalcitonin, SII [17], coagulation function (prothrombin time, activated partial prothrombin time, bleeding time), liver function (alanine transaminase, glutamic transaminase, lactate dehydrogenase, total bilirubin, direct bilirubin), renal function (creatinine, uric acid, eGFR), high-sensitivity troponin T, serum B-type natriuretic peptide, myocardial enzyme (creatine kinase, creatine kinase MB isoenzyme), and other laboratory examination of blood;Chest X-ray (for pulmonary inflammation and effusion, etc.), CTA scan of the cervical, thoracic, and abdominal aorta artery (for aortic diameter and extent of dissection, etc.), cardiac ultrasound (for cardiac ejection fraction and left ventricular diastolic dysfunction, etc.), and other imaging examinations.The patient’s cardiopulmonary bypass time during surgery, total surgical time, aortic cross-clamping time, and postoperative hospital stay;Postoperative drainage color, drainage volume, postoperative patient blood transfusion, and transfusion volume;The incidence of postoperative sternal infection, secondary debridement, secondary tracheal intubation, pneumonia, and delirium; andEnzyme-linked immunosorbent assay (ELISA) will be performed to detect and measure IL-1β IL-2, IL-4, IL-6, IL-8, IL-10, IL-12, IL-13, TNF-α, INF-γ, granulocyte–macrophage colony-stimulating factor (GM-CSF) and calcitonin;

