### Intervention description {11a}

The surgeries will be performed by [name]. The study will commence on the day the patients sign an informed consent form and receive their randomized numbers. The ketorolac group, consisting of patients with aTAAD, will be treated with ketorolac. They will receive a preoperative intramuscular injection of 60 mg per 2 ml ketorolac and a postoperative injection of 30 mg per 1 ml ketorolac BID for two consecutive days. The placebo group, also consisting of patients with aTAAD, will receive placebo treatment. They will receive a preoperative intramuscular injection of 2 ml 0.9% saline placebo and a postoperative injection of 1 ml 0.9% saline placebo BID for two consecutive days. During the administration of ketorolac, patients’ blood pressure and renal function will be routinely monitored, and targeted treatment methods such as sedation, hypotension, diuresis, and dialysis will be applied as necessary. Additionally, all included patients will receive the same medical and surgical treatments in accordance with the diagnosis and treatment guidelines for aTAAD. Aortic dissection tissue samples will be collected for laboratory study during the surgery. Both the ketorolac group and the placebo group patients will undergo follow-up examinations before surgery and on the 1st, 3rd, 5th, 7th, 30th, and 90th day after surgery. These examinations will include assessments of adverse drug events, cardiac ultrasound, chest X-ray, laboratory tests (blood routine examination, blood biochemistry, erythrocyte sedimentation rate, coagulation function, CK-MB, cardiac troponin I (cTnI), PCT, IL-6, CRP, myohemoglobin (MYO), type B natriuretic peptide (BNP), D-dimer, etc.) and clinical biomarkers (matrix metalloproteinase-9 (MMP-9), MMP-2, MMP-3, MMP-13, type III procollagen, etc.). CTA examination of the cervical, thoracic, and abdominal aorta artery will be performed before surgery and on the 30th and 90th days after surgery.

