### Methods in analysis to handle protocol non-adherence and any statistical methods to handle missing data {20c}

We allow patients to have 10% missing data, which will be deleted as blank. When the patient’s data is missing by more than 10%, the patient will be deleted.

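### Day-30 and day-90 imaging endpoints treat death as ordinary missing data, so survivors are tested as if they were the randomised groups

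*Protocol article*

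**What the plan says.** The Secondary endpoints section of the protocol article lists "CTA scan of the cervical, thoracic, and abdominal aorta artery (for aortic diameter and extent of dissection, etc", together with cardiac ultrasound for ejection fraction and diastolic function.

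On timing, Intervention description {11a} states: "CTA examination of the cervical, thoracic, and abdominal aorta artery will be performed before surgery and on the 30th and 90th days after surgery". Table 1 agrees for CTA and puts echocardiography before surgery and on days 3, 30 and 90.

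On absent data, section {20c} says: "We allow patients to have 10% missing data, which will be deleted as blank". Its next sentence deletes any patient above that threshold. Section {20a} gives up intention to treat for this reason. It assigns continuous variables to a t-test or Mann-Whitney test and categorical ones to chi-square or Fisher. Neither section separates death from other reasons for a missing value.

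On how common death may be, Sample size {14} cites the literature: "the total death rate of hospitalization after surgery was 25% [7]". Death is also a component of the primary efficacy endpoint under Outcomes {12}.

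**The concern.** A day-30 or day-90 aortic diameter does not exist for a patient who died on day 10. It is not a value that was there and went unrecorded. Under the stated rules such a patient drops out of the imaging comparison, either as a blank or by deletion, and a two-sample test is run on those who remain. Randomisation protects the comparison of all patients allocated. It does not protect a comparison of those who lived long enough to be scanned when treatment may affect who lives, and this trial is designed on the expectation that treatment affects a composite that includes death.

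Two things are at stake. CTA is the only scheduled follow-up measure of aortic anatomy, and the Background rests partly on animal findings that ketorolac slows aortic disease. A p-value on survivors could be read as randomised evidence on that mechanism. In addition, deleting a whole patient removes more than the scan: it takes out the earlier measurements and, on the text, possibly the death itself.

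**Working it through.** **1. The plan's own sample size.** Inputs from Sample size {14}: 70% versus 40%, power read as 90%. Two-sided alpha of 0.05 comes from {20a}. With unpooled variance:

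n = (1.960 + 1.282)² × (0.7×0.3 + 0.4×0.6) / 0.3² = 52.5, so 53 per arm. This matches the plan. Sixty per arm allows 1 − 53/60 = 11.7% loss. The design figure is not in question here; it fixes the 60 per arm used below.

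**2. How many patients have no late scan.** At 25% deaths, 0.25 × 60 = 15 control patients would be unscanned, leaving 45. *Assumption:* ketorolac deaths fall in the same proportion as the composite, 25% × 40/70 = 14.3%, or 8.6 of 60, leaving 51.4. No section states a mortality effect.

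**3. Blanked or deleted?** Assessment marks per patient in Table 1: vital signs 8, haematology 8, CTA 3, chest X-ray 6, echocardiography 4, adverse events 8, complications 8; total 45.

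| Time of death | Marks lost | Share |
|---|---|---|
| after day 3, before day 5 | 24/45 | 53% |
| after day 7, before day 30 | 14/45 | 31% |
| after day 30, before day 90 | 7/45 | 16% |

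If the 10% is counted over these scheduled assessments, every death before day 90 exceeds it and the patient is deleted. The article does not say how the 10% is counted.

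**4. Size of the survivor shift.** *Assumptions:* a standard normal frailty determines death; it has correlation ρ with the imaging value (higher is worse); there is no true imaging effect. The mean imaging value in survivors at mortality p is −ρ φ(c)/(1 − p), where c is the (1 − p) normal quantile.

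- p = 25%: φ(c)/(1 − p) = 0.424
- p = 14.3%: φ(c)/(1 − p) = 0.263
- Difference: 0.160 × ρ

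Ketorolac minus control, in SD, with control mortality at 25% (positive counts against ketorolac):

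| Ketorolac mortality | ρ = 0.3 | ρ = 0.5 | ρ = 0.7 |
|---|---|---|---|
| 14.3% | 0.048 | 0.080 | 0.112 |
| 20% | 0.022 | 0.037 | 0.052 |
| 25% | 0 | 0 | 0 |
| 30% | −0.022 | −0.037 | −0.051 |

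In the first row the standard error is √(1/45 + 1/51.4) = 0.204 SD, so the shift is 0.048/0.204 = 0.24 to 0.112/0.204 = 0.55 standard errors.

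**5. What a worst-rank test does.** Simulation with 60 per arm, a true imaging benefit of 0.5 SD, ρ from 0.3 to 0.7 and 2,000 runs per setting:

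| Mortality, control vs ketorolac | Power, survivors only | Power, deaths ranked worst |
|---|---|---|
| 25% vs 14.3% | 53–60% | 70–74% |
| 25% vs 25% | 65–73% | 32–39% |

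Ranking deaths worst gains power when the drug also reduces deaths and loses about half of it when mortality is equal.

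**The case against.** The strongest reply has four parts.

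- **The handling of secondary imaging endpoints is usually left to the analysis plan.** That would answer a complaint about silence. Sections {20a} and {20c} are not silent: they state a rule, and it is the wrong one for values that death makes impossible.
- **The effect is small and its inputs are assumed.** This stands. The 25% is a literature in-hospital rate. The Eligibility criteria exclude preoperative malperfusion, mechanical assistance, intubation and patients over 65, so the trial's own mortality may be lower. The 14.3% and the correlations appear in no section. Even on these inputs the shift is at most about half a standard error.
- **A worst-rank test as the main analysis could do more harm than the defect.** This also stands. With equal 25% mortality its power is roughly half that of the survivor comparison, and it partly re-tests death, which the primary composite already counts. A survivor analysis that is labelled as such, with deaths shown, is legitimate.
- **The direction is not known.** A reader might infer that the plan hides part of any benefit. The documents do not support that. Masking requires both that ketorolac lowers mortality and that the patients it saves have worse imaging. With equal mortality there is no shift in this model, and with higher ketorolac mortality the shift favours the drug.

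A reader might also infer that day-3 ejection fraction needs special scoring, because Sample size {14} cites 20% for mechanical support. That is a literature figure for needing support after surgery. No section says how many patients would still be supported on day 3, so the inference has no basis here.

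**Conclusion.** The point holds in a limited form. The stated rules treat death as ordinary missing data, so day-30 and day-90 CTA and echocardiography are tested in survivors as though those were the randomised groups. If mortality differs between arms, the result can be biased either way. Under 25% versus 14.3% mortality and correlations of 0.3 to 0.7 the shift is about 0.05 to 0.11 SD against ketorolac; at 30% ketorolac mortality it is about 0.02 to 0.05 SD in its favour; at equal mortality it is zero. All of these rest on the assumed model.

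The deletion rule makes matters worse. On the Table 1 count it could remove every patient who dies before day 90, but this depends on how the 10% is counted, which the article leaves open. That the primary composite will lose its deaths is therefore a possible reading, not an established one. The t-test and Mann-Whitney part concerns continuous measures only; categorical findings go to chi-square or Fisher but have the same survivor restriction. These endpoints are secondary and the bias is modest. It should be corrected before unblinding, but it does not undermine the design.

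**What to change.** 1. In {20c}, exempt patients who die from the deletion rule, so that their earlier data and their death stay in the analysis.
2. In {20a}, describe day-30 and day-90 comparisons of continuous CTA and echocardiographic measures as survivor-only and descriptive. Show beside each the number dead and the number alive but unscanned, per arm.
3. Add, as a sensitivity analysis only, a Mann-Whitney test on all randomised patients with deaths before the scan ranked worst.

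The cost is analysis wording; no new data or visits are needed. The downside lies in item 3: the ranked result mixes death with imaging and loses power if mortality is equal (32–39% against 65–73% in the 25% scenario). It should therefore be neither the sole nor the main test, and the survivor values should stand next to it.

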## Introduction

### Background and rationale {6a}

Acute type A aortic dissection (aTAAD) is considered the most perilous form of aortic disease [1]. Common causes include hypertension, medial degeneration (cystic medial necrosis), and Marfan syndrome [2]. Currently, rapid surgical reconstruction remains the primary treatment option for aTAAD [3–6]. Based on reported references, the in-hospital mortality rate after surgery stands at 25% [7]. Consequently, there is a pressing need to investigate alternative approaches that can effectively decrease surgical mortality.

Previous studies have shown that activated macrophages in mice secrete inflammatory factors, which can enhance migration and invasion capabilities, accelerate degradation of the aortic media, and contribute to the development of type A aortic dissection (TAAD) [8–10]. Additionally, Rho GTPase, an important regulator of cytoskeleton actin and intracellular signal transduction, has been found to be activated in TAAD [11, 12]. In the literature, it has been observed that ketorolac, a nonsteroidal anti-inflammatory drug and inhibitor of the Rho GTPase signaling pathway, can reduce the progression, incidence, and severity of aortic disease in animal models [13, 14].

Previous clinical research has suggested that ketorolac may reduce postoperative mortality, neurological complications, renal complications, and respiratory failure in patients undergoing open abdominal aortic aneurysm replacement surgery [15]. However, it is important to note that this study was retrospective and focused specifically on abdominal aortic aneurysm. Additionally, the 2022 American Heart Association (AHA) guidelines have reported controversy regarding the use of ketorolac in the analgesic treatment of aTAAD [16]. Therefore, our plan is to conduct a single-center, randomized, double-blinded, and placebo-controlled trial to investigate the safety and efficacy of ketorolac in improving the prognosis of aTAAD patients.

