## Statistical methods

### Statistical methods for primary and secondary outcomes {20a}

Statistical analysis will be performed using SPSS software (version 26.0) and R (× 64 3.5.0). Continuous variables will be presented as mean ± standard deviation. The Kolmogorov–Smirnov test will assess normal distribution. If variables exhibit normal distribution, an independent sample *t*-test will be employed; otherwise, the Mann–Whitney *U* test will be utilized. Categorical variables’ frequency will be expressed as percentages and analyzed using the chi-square test or Fisher’s exact test. It should be noted that we are not conducting an Intention to Treat analysis due to the exclusion of patients with more than 10% missing data. Double-tailed *p*-values and 95% confidence intervals will be reported, with statistical significance defined as *p* < 0.05.

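### Postoperative hospital stay is to be compared by t-test or Mann–Whitney with no rule for in-hospital deaths, so a survival benefit can appear as a longer stay, or the comparison is confined to survivors

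*Protocol article*

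**What the plan says.** Under Secondary endpoints, the protocol article lists cardiopulmonary bypass time together with "total surgical time, aortic cross-clamping time, and postoperative hospital stay". No definition of stay follows.

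Section {20a} gives the test for continuous variables: "If variables exhibit normal distribution, an independent sample *t*-test will be employed; otherwise, the Mann–Whitney *U* test will be utilized". Stay is not excepted.

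Deaths are expected. Section {14} cites from the literature that "the total death rate of hospitalization after surgery was 25" per cent, and section {6a} gives the same figure. Death also opens the primary composite: "Efficacy: death, organ malperfusion syndrome, permanent dialysis, tracheotomy, neurological impairment".

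Sections {20a} and {20c} remove any patient with more than 10% missing data. They do not say whether assessments that never took place because the patient had died count as missing. The article contains no worst-rank rule, competing-risk analysis or stated survivor-only analysis for stay.

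**The concern.** Death ends a hospital stay. If stay is the number of days from surgery until the patient leaves the ward for any reason, a death on day 3 counts as shorter than a discharge home on day 18. The measure then moves against the arm with fewer early deaths, and fewer deaths is one of the effects the trial hopes to find. A reader could see a favourable composite beside an apparently longer stay and take the second as a cost of treatment.

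Leaving the deaths out does not solve this. Survival is itself an outcome that the drug may change, so the survivors in the two arms are no longer groups formed by randomisation.

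This is more than detail left to an analysis plan. The article already fixes the tests and a deletion rule, and neither way of applying them to stay gives a sound comparison.

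**Working it through.** **The plan's own figures.** The article gives none for stay. Its only calculation is for the composite (70% versus 40%), which reproduces with unpooled variance: (0.70×0.30 + 0.40×0.60) × (1.960 + 1.282)² / 0.30² = 52.5, so 53 per arm. Hospital stay plays no part in it.

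**Number of deaths.** At the cited 25%, 0.25 × 60 = 15 control patients would die in hospital.

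**Route A: deaths entered at the day of death.**

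Assumed inputs, none from the article:
- survivors' stay is log-normal, median 18 days, log-SD 0.4, identical in both arms;
- time to death is log-normal, log-SD 0.7, with the median varied;
- mortality is 25% (control) and 15% (ketorolac), with 60 per arm.

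Mean survivor stay is 18 × exp(0.4²/2) = 19.50 days. Mean time to death is the median × exp(0.7²/2) = median × 1.278. The expected difference in mean stay (ketorolac minus control) is (0.25 − 0.15) × (19.50 − mean time to death).

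For Mann–Whitney, the probability that a ketorolac patient has the longer stay is 0.5 + (0.25 − 0.15) × (P − 0.5). Here P is the chance that a survivor's stay exceeds a time to death: P = Φ(ln(18/median) / √(0.4² + 0.7²)).

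| Median death day | Mean time to death | Difference in mean stay | P | Probability ketorolac longer | Mann–Whitney significant for longer stay |
|---|---|---|---|---|---|
| 5 | 6.39 | +1.31 days | 0.944 | 0.544 | about 13% |
| 10 | 12.78 | +0.67 days | 0.767 | 0.527 | about 8% |
| 15 | 19.16 | +0.03 days | 0.589 | 0.509 | about 4% |
| 18 | 23.00 | −0.35 days | 0.500 | 0.500 | about 2.6% |

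The last column is simulated (3,000 to 4,000 trials per row); the nominal value in that direction is 2.5%. Simulated mean differences for the first three rows were about +1.3, +0.65 and +0.06 days, which agree with the formula within simulation error.

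Other settings, with deaths at median day 5:
- 25% versus 25%: about 2 to 2.5%, no distortion.
- 25% versus 10%: about 24%, +2.0 days.
- 15% versus 9%: about 7%, +0.8 days.

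A second set of assumptions gives a similar picture. With median survivor stay 16 days, deaths at median day 3, and mortality 25% versus 14.3% (25% × 40/70), mean stay is 14.3 versus 15.8 days and 14.9% of trials are significant for a longer stay on ketorolac. With deaths ranked worst in the same model, 17.5% are significant in favour of ketorolac. With mortality again 25% versus 14.3% but deaths at median day 4, a 10% shortening of survivors' stay on ketorolac cancels the reversal.

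**Route B: deaths deleted.** Section {11a} schedules seven examinations: before surgery and on days 1, 3, 5, 7, 30 and 90. A patient who dies before day 30 misses at least 2 of 7, or 29%, which is above 10%. If such data count as missing, the patient is removed and only survivors are compared. The size of the resulting bias depends on how sick the additional survivors are, and the article gives no basis for a figure.

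**The case against.** Four stronger readings are tempting, and the article does not support them.

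- *The plan scores early deaths as short stays.* It does not say so. Section {20a} names tests, not the value a death receives, and the deletion rule may remove these patients instead. This objection stands; it is why both routes are set out above.
- *The trial assumes that 25% of its patients die in hospital.* The 25% is a literature figure. What section {14} assumes is the composite: "we assumed that the incidence of composite endpoint events in the control group is 70" per cent, falling to 40%. Section {10} excludes patients over 65 and those with malperfusion, preoperative intubation or mechanical support, so mortality here may be lower. Section {14} does, however, carry the figure unadjusted.
- *A survival benefit would look like harm.* It can. The article gives no timing of death, and the reversal fades to nominal once deaths come about as late as discharges. Even at 25% versus 10% with early deaths, about 76% of simulated trials show no significant reversal.
- *All the dates for a better measure are already collected.* Section {18a} records data from hospital visits and a closing telephone interview. It does not list discharge, readmission and death dates, so this is an inference.

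It is also fair to say that days alive and out of hospital largely restates mortality. With the same survivor stay in both arms, its difference is about 0.10 × (90 − 19.5) = 7 days at 25% versus 15%. Its advantage in this illustration therefore follows from the assumptions and is not independent evidence.

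These points limit the size. They do not supply a valid rule for deaths.

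**Conclusion.** The point holds in this form: the article fixes the test for postoperative stay, cites substantial in-hospital mortality, and leaves open how deaths enter. Both available routes are unsound, one because an early death counts as a short stay and the other because it conditions on survival.

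Under the main assumptions at 25% versus 15%, the distortion runs from about +1.3 days with 13% wrong-direction significance (deaths at median day 5) to almost nothing with 4% (median day 15). Lower mortality, a smaller survival difference or a real shortening of survivors' stay would reduce it. The direction and mechanism for early deaths are certain; the size in this trial is not.

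The effect is confined to one secondary endpoint among many. The sample size and the test of the primary composite are untouched. The point should be settled, because a rule chosen after unblinding could change the direction of the result.

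**What to change.** Before unblinding, replace raw stay in the between-arm test with one of:

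1. days alive and out of hospital to day 90, deaths scored 0, compared by Mann–Whitney;
2. time to discharge alive, with in-hospital death as a competing event (cumulative incidence, Gray's test);
3. postoperative stay with in-hospital deaths ranked as the worst outcome, compared by Mann–Whitney.

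State that, for this endpoint, data lost to death do not count as missing under the 10% deletion rule. Show raw stay in survivors as description only.

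The cost is a sentence or two in the endpoint and analysis text. The first option is less familiar than length of stay, partly repeats mortality, and needs discharge, readmission and death dates. These should be obtainable from the 90-day follow-up in section {18a}, but the case report form should be checked for them. Options 2 and 3 need only the date and manner of leaving hospital.
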